### Implementation and dissemination

When the efficacy of the digital health application can be demonstrated, permanent reimbursement within the German Digital Healthcare Act is pursued. With permanent reimbursement, widespread implementation of the application into clinical practice can be achieved. Furthermore, the results on the efficacy will be shared with health insurance companies as well as healthcare professionals to allow the widespread dissemination of results.

## Discussion

In this article, we present the study design of a multicenter, open-label, randomized, parallel-group, controlled trial to evaluate the health care effects and medical benefits of a smartphone-based diabetes self-management app. Outcome measures will comprise both direct medical benefits on blood glucose levels, HbA1c, and quality of life as well as patient-reported outcomes relevant for the health behavior of people with diabetes such as treatment adherence, patient autonomy, and coping with illness-related difficulties in everyday life.

We decided to initiate a prospective randomized, controlled study to potentially prove the causation of benefits and effects and to enhance evidence by randomization of patients and intention-to-treat analyses [41]. This study is intended to confirm the findings of a retrospective systematic analysis of 5920 mySugr PRO users (57.8% people with type 2 diabetes), as required by the Digital Healthcare Act. In this study, the largest group (*n* = 3836, initial eHbA1c < 7.5%) showed a stable eHbA1c of around 6.4% over 3 and 6 months. In the subgroup with initial eHbA1c > 9%, eHbA1c levels decreased by 1.5% and 1.7% after 3 and 6 months, respectively [27]. Since HbA1c analysis is generally accepted to provide evidence on the average blood glucose level during the previous 8 to 12 weeks [42], we concluded that the 12-week duration of the study period should be sufficient to demonstrate effectiveness. Furthermore, the criteria of the Digital Healthcare Act require the final study report to be completed within 12 months after the beginning of recruitment [26]. A longer follow-up period would therefore not be feasible. Likewise, the choice of the control group (treatment-as-usual) seems to be appropriate because no other digital application for diabetes self-management has been assessed in an approach meeting comparable scientific and methodological requirements so far.

As outcome measures, we will not only assess the direct medical effects on blood glucose and HbA1c levels because of their relationship with diabetic complications [43, 44] but also several PRO assessing psychological aspects of diabetes that have been shown to be important to people with diabetes [45, 46]. Preliminary evidence for the beneficial effects of mySugr on specific PRO was obtained in a retrospective systematic analysis, which was conducted during the application process for the Digital Healthcare Act. In this study, the comparison of 1099 study participants using the app with a historical cohort of 824 non-users revealed significantly decreased PAID-5 scores in app users with type 1 or type 2 diabetes (overall sample, 6.32 ± 4.36 vs. 5.07 ± 4.20, *t*(1921) = 6.36, *p* < 0.001; type 1 diabetes, 6.55 ± 4.30 vs. 5.12 ± 3.96, *t*(815) = 4.85, *p* < 0.001; type 2 diabetes, 6.01 ± 4.42 vs. 4.96 ± 4.23; *t*(1066) = 3.75, *p* < 0.001) [27]. Therefore, diabetes distress will be evaluated as the primary endpoint by the PAID questionnaire [33], a widely accepted scale to assess diabetes distress, since its results are associated with the functionality of coping styles, quality of life, and the occurrence of depressive symptoms [47]. Diabetes distress is common among people with diabetes, with a prevalence of approximately 20 to 40% [48, 49] and 36%, respectively [12]. Diabetes distress hinders the optimal management of diabetes and impacts on the emotional well-being, self-care, and quality of life of people with diabetes [13, 50] and, therefore, represents an important and valid outcome measure [51–53]. The broad spectrum of secondary endpoints then aims at reflecting the complexity of diabetes therapy and care that includes the self-management of dietary control, physical activity, and health care use, as well as diabetes-specific empowerment, self-efficacy, and satisfaction with current treatment. There is a great body of evidence that corresponding PRO are clinically relevant as they are associated with glycemic parameters [54], which is particularly true for PRO measures such as diabetes distress and self-management behaviors [13, 47, 50, 55].

We recognized the lack of blinding as a major limitation of our study design that might affect the generalizability of results. Obviously, blinding to reduce bias due to the knowledge of which intervention is being received is not possible in this setting. However, we believe that the impact of this limitation will be low for three reasons. First, the frequency of visits (beginning and end of study) prevents clinicians from reflecting their opinions on the allocation of participants and potential outcomes to people with diabetes. Second, the intervention will be used in the private environment of people with diabetes and independently from the health care provider. Third, outcomes will be correlated, for example, with the frequency of and the satisfaction with app usage, and the potential influence of these and other variables will be assessed by statistical mediation analysis.

In conclusion, this study aims to evaluate if diabetes distress can be reduced by the use of a smartphone-based diabetes self-management app (mySugr PRO) when compared to the control group. We will further assess if the use of the app supports the diabetes self-management of people with diabetes in several aspects relevant to medical and health care outcomes. In summary, this study will provide valuable insights into the efficacy of a digital health application in people with diabetes in a methodologically sound randomized controlled trial.

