### Randomization, sequence generation, and blinding

Randomization will be performed by a computer-generated randomization sequence (Research Randomizer [32]), assigning participants to the interventional or control group in a 2:1 ratio, by block randomization with an initial block size of six and three for subsequent participants. Study centers will receive concealed envelopes with the randomization results for each participant separately. The respective envelope will be opened by the study staff at the first study visit of the participant, and the participant will be allocated accordingly. Due to the nature of the intervention, blinding of participants and study centers providing the intervention will not be possible.

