### Procedures

As depicted in Fig. 1, our study will comprise a 12-week study period that starts and ends with study visits for baseline and follow-up examinations. At study visit 1, participants will be allocated to the study groups according to randomization after informed consent is given. Blood glucose meters from all participants will be read out. Participants of the interventional group will download both the mySugr PRO application (mySugr GmbH, Austria) and the application for mobile EMA capturing time-varying real-life experience (mEMA, ilumivu, USA). Applications will be used via pseudonymized study accounts. Baseline examination at visit 1 will then involve the collection of blood glucose data and the completion of questionnaires on patient-reported outcomes (PRO, see below). Blood glucose data comprise the self-monitored average glucose levels, the corresponding percentages of hypoglycemic (< 70 mg/dl; < 54 mg/dl), euglycemic (70–180 mg/dl), and hyperglycemic (> 180 mg/dl) values, as well as the last documented or routinely assessed HbA1c. During the 12-week study period, participants of the interventional group will use mySugr PRO for diabetes self-management, while control patients will continue with their present mode of self-management. Additionally, participants of the interventional group will daily report their real-world experience via mEMA, both at the beginning and at the end of the interventional phase over a period of 10 days each. Follow-up examination at visit 2 will assess the same data as the baseline evaluation at visit 1, extended by an additional questionnaire on the perceived quality of the intervention and treatment satisfaction (interventional group). Adverse events and serious adverse events will be documented throughout the study. There will be no provisions for ancillary and post-trial care, and there will be no post-trial compensation since we expect no harm due to trial participation.

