### Patient-reported outcomes

At visits 1 and 2, all participants will complete the following PRO questionnaires. As the primary endpoint, the Problem Areas In Diabetes (PAID) questionnaire contains 20 items on areas of diabetes-related psychosocial distress to be rated on a 5-point Likert scale [33]. As secondary endpoints, questionnaires on diabetes self-management, diabetes-specific empowerment, general well-being, self-efficacy expectation, and treatment satisfaction will be completed at visits 1 and 2. In detail, the Diabetes Self-Management Questionnaire (DSMQ) presents a 16-item self-report scale on glucose management, dietary control, physical activity, and health care use, with each item to be rated on a Likert scale ranging from 0 (does not apply) to 3 (very much applies) [34]. The questionnaire on diabetes-specific empowerment bases on the German version of the diabetes empowerment scale (DES; 11 items to be rated on a 4-point scale; [35]). General well-being will be assessed by the WHO-5 scale, in which patients will be required to rate how well each of five statements applies when considering the last 14 days [36]. The questionnaire on general self-efficacy (GSE) contains 10 items to be rated on a 4-point Likert scale [37]. For the evaluation of diabetes treatment satisfaction, we used the questionnaire for the assessment of diabetes-related problems and satisfaction with insulin treatment (DSat; [38]). The DSat questionnaire has 10 questions, each of which is scored on a scale ranging from 1 (very satisfied) to 6 (completely dissatisfied). The topics of this questionnaire include satisfaction with glucose levels, flexibility, and hypoglycemia. At visit 2, participants of the interventional group will additionally complete an adapted version of the Mobile Application Rating Scale (MARS) to assess the perceived quality of the intervention [39]. All primary and secondary outcomes are depicted in Fig. 2.

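### Having only two visits does not shield the PAID from open-label bias, because both ratings are made at those visits, and the baseline rating is listed after allocation is known

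*Protocol article*

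**What the plan says.** All references are to the protocol article.

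- **Blinding.** Randomization, sequence generation, and blinding states that "blinding of participants and study centers providing the intervention will not be possible". On allocation: "The respective envelope will be opened by the study staff at the first study visit of the participant".
- **Visits.** Procedures: "our study will comprise a 12-week study period that starts and ends with study visits for baseline and follow-up examinations". No other study visit is described.
- **Primary endpoint.** Patient-reported outcomes: "At visits 1 and 2, all participants will complete the following PRO questionnaires". The primary instrument is among them: "the Problem Areas In Diabetes (PAID) questionnaire contains 20 items on areas of diabetes-related psychosocial distress". It is self-rated.
- **Order at visit 1.** Procedures lists consent and allocation, then meter read-out in everyone, then app download in the intervention group. After these, the baseline examination "will then involve the collection of blood glucose data and the completion of questionnaires on patient-reported outcomes".
- **Order at visit 2.** "Follow-up examination at visit 2 will assess the same data as the baseline evaluation at visit 1". The intervention group also completes the app-quality questionnaire (MARS). No sequence is given.
- **Reassurance.** The Discussion calls the lack of blinding a major limitation but expects a low impact for three reasons. The first is that "the frequency of visits (beginning and end of study) prevents clinicians from reflecting their opinions on the allocation of participants and potential outcomes". The second is that the app is used privately, away from the health care provider. The third is that outcomes will be related to app use and satisfaction, with mediation analysis.

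**The concern.** Few visits limit contact between measurements. They offer nothing at the moment of measurement if the measurement is made during the contact. Here the only two contacts with an unblinded site are also the only two occasions on which the PAID is completed, so the article's own schedule undercuts the safeguard it claims.

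The stated order at visit 1 adds a second problem. A baseline covariate should be fixed before the participant knows the arm. As listed, the baseline PAID follows the opening of the envelope and, in one arm only, the installation of the app. Relief or disappointment at the allocation can enter the covariate.

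What is at stake is the gatekeeping test. The PAID stands first in the hierarchical sequence in Statistical analysis, so a spurious result there opens HbA1c and the later endpoints to testing. Implementation and dissemination ties demonstrated efficacy to permanent reimbursement. A reader who accepts the reassurance would discount a bias that nothing in the described procedure limits.

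**Working it through.** **1. Contact and measurement side by side**

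| Occasion | Site knows arm | Participant knows arm | PAID completed |
|---|---|---|---|
| Visit 1, as listed | yes, envelope opened | yes | yes, listed after allocation, read-out and app download |
| Between visits | – | yes | no |
| Visit 2 | yes | yes | yes, order not stated |

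The interval that the first reason protects contains no PAID measurement.

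**2. Do the other two reasons fill the gap?** Private use of the app does not change where the PAID is completed. App use and satisfaction with the app arise after randomization and exist only in the app arm. A participant who is pleased with the app may report less distress for that reason alone, so mediation analysis on these variables cannot separate reporting bias from an app effect.

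**3. The plan's sample size (not disputed).** Inputs from Study population: 0.3 SD, two-sided alpha 0.05, power 0.80, 2:1 allocation, 15% drop-out.
- Normal approximation: control n = (1 + 1/2) × (1.960 + 0.842)² / 0.3² = 130.8, so 131 control and 393 in total.
- Noncentral t: 132 + 264 = 396, power 0.802. This is the stated 396.
- Drop-out: 396 / 0.85 = 465.9, so 466, split 311 and 155. This matches.

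**4. What a reporting shift would do (illustration).** The documents give no size, so the shift b is an assumption. With no true effect:
- SE = √(1/132 + 1/264) = 0.1066 SD. The smallest significant difference is 1.96 × 0.1066 = 0.209 SD.
- P(significant, favouring the app) = 1 − Φ(1.96 − b/SE).

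| Assumed b (SD) | P favouring the app | Share of planned 0.3 SD |
|---|---|---|
| 0 | 2.5% | 0 |
| 0.05 | 6.8% | 1/6 |
| 0.10 | 15.3% | 1/3 |
| 0.15 | 29.0% | 1/2 |

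The planned analysis is ANCOVA. If the baseline–follow-up correlation r is 0.5 to 0.7 (assumed), the SE becomes 0.1066 × √(1 − r²), and b = 0.10 gives 19.0% to 25.9%.

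**5. The affected baseline.** The ANCOVA estimate is (follow-up difference) − slope × (baseline difference). With equal SDs the slope is about r. If knowledge of the arm moved the baseline difference by an assumed 0.10 SD, the estimate would move by 0.5 × 0.10 = 0.05 to 0.7 × 0.10 = 0.07 SD. The direction is unknown: a lower baseline rating in the app arm would shrink the apparent benefit, and a higher one would enlarge it.

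**The case against.** The strongest objection is that this is a condensed article. The Clinical Investigation Plan and the visit figure are not shown, and order within a visit is normally a matter for them or for a site manual. That holds for visit 2, where silence is not a defect. It does not hold for the Discussion, which makes a positive claim, or for visit 1, where the article itself gives a sequence. The full plan may set a different order, in which case the article should say so.

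The limitation is also disclosed openly. True, but the disclosure is paired with a reassurance that does not follow.

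A reader might infer more: that at visit 2 unblinded staff read the meter, tell the participant the results, and only then hand out the PAID. The documents do not support this. Visit 2 is defined by the data collected, not by sequence. No section says that results are shown or withheld. The HbA1c is the last documented or routine value, so nothing new need emerge at the visit. Read-out is common to both arms, so its position alone does not favour either one. If better glucose lowers distress, that is arguably part of the app's effect.

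Finally, the rejection probabilities describe any shift of the assumed size, whatever its source. Participants would still know their arm after re-ordering, so the figures cannot be credited to the fix. This objection stands in full.

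**Conclusion.** The point holds in a limited form. The Discussion's first reason gives the PAID no protection when it is rated, and the other two reasons do not supply it. The visit 1 order, as written, has the baseline PAID completed with the arm known. Both conclusions rest on the article's text alone and need no assumption.

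The size of the resulting bias is unknown. Shifts of 0.05 to 0.15 SD would be one sixth to one half of the planned effect and would raise the chance of a false result favouring the app from 2.5% to about 7% to 29%. These shifts are assumed and the calculation ignores any gain from the covariate. The claim that glucose results are disclosed before the visit 2 PAID is not established and forms no part of this conclusion. No sample-size figure changes. The correction is worth making because it is cheap and concerns the endpoint that gates all the others. It reduces an unavoidable open-label problem without removing it.

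**What to change.** **Procedures, visit 1.** State that the PAID and the other questionnaires are completed after consent, but before the envelope is opened and before the meter is read out.

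**Procedures, visit 2.** State that the questionnaires are completed first, by the participant alone, before contact with the clinician, before read-out or any discussion of results, and before the MARS in the app arm.

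**Discussion.** Delete the first reason or replace it with this safeguard, and acknowledge that reporting bias from participants knowing their own arm remains.

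**Cost.** One paragraph and a site instruction, with no added visit, instrument or participant. Sites must hand out the questionnaires on arrival. Recruitment began in February 2021, so a change during the trial would mix two measurement conditions, in some participants between baseline and follow-up. Those already measured under the previous order should be noted. If sites already work in the proposed order, one sentence saying so is enough. The Discussion can be corrected at any stage.

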## Trial status

The protocol version number is 1.3, 21.12.2020. The protocol was amended to reflect the deletion of a questionnaire on physician satisfaction and inclusion of an updated version of the quality management system of the application. The recruitment began on February 11, 2021. Recruitment is expected to be completed on May 31, 2022, with the last-patient-last-visit at the end of August 2022.

## Data Availability

Not applicable; this is only a study protocol, and as such, no unpublished data are available.

## Abbreviations

BfArM: German Federal Institute for Drugs and Medical Devices (Bundesinstitut für Arzneimittel und Medizinprodukte)
CGM: Continuous glucose monitoring
DES: Diabetes Empowerment Scale
DiGA: Digital Health Application (digitale Gesundheitsanwendung)
DSat: Questionnaire for the assessment of diabetes-related problems and satisfaction with insulin treatment
DSMQ: Diabetes Self-Management Questionnaire
eHbA1c: Estimated HbA1c
GSE: General Self-Efficacy
MARS: Mobile Application Rating Scale
mEMA: Mobile ecological momentary assessment
PAID: Problem Areas In Diabetes
PRO: Patient-reported outcomes
